### 3.8. Other Outcome Measures

#### 3.8.1. The Expression of HPA Axis-Related Hormone Factors and Inflammatory Cytokines

Blood samples of CRF patients in the acupuncture group and the basic treatment group will be collected for testing before and 3 weeks after treatment, respectively. Fast-fasting blood samples will be collected from all subjects in the morning. And the collected samples will be centrifuged at 3000 rpm at 4°C for 15 min. Moreover, Serums will be collected and stored at -80°C. Human serum CORT, ACTH, IL-6, IL-1*β*, and TNF-*α* enzyme-linked immunosorbent assay kit will be used for detection. In addition, the ELISA kit will be balanced at room temperature for 30 min, and the samples will be dissolved at room temperature. Standard samples with different gradient concentrations will be prepared, and a standard diluent will be added. We will add 50 *μ*l of biotin-binding antibody to each well, seal the plates, place in a horizontal shaker to shake slightly and mix, and incubate at room temperature for 2.5 h. We will discard the supernatant, add the detection antibody, and incubate at room temperature for 1 h. We will discard the supernatant and incubate in the dark at room temperature. Then, we will add the stop solution and, after fully mixing, detect the absorbance OD value at 450 nm with the enzyme plate analyzer.

#### 3.8.2. The Changes in Gut Microbiota

Fecal specimens will be collected before and 3 weeks after treatment for detection. The subjects should collect the feces immediately after defecating in the morning to ensure the feces are fresh. Then, the central part of the feces should be collected by using sterile cotton swabs, and contact with the feces should be avoided. The amount of feces should be collected as much as possible. Subsequently, we will put fresh feces in a sterile feces box and immediately put the feces box in a -80°C refrigerator for preservation. The feces will be taken out of the refrigerator and placed on ice. 200 mg of feces will be taken out and put into a sterile centrifuge tube. The DNA of gut microbiota from the feces samples will be extracted, and the purity of DNA will be measured by the A260/280 method. Then, primers will be found according to 16SrDNA sequences of gut microbiota, and a BLAST GenBank will be used to compare the specificity of the primers for PCR amplification. Subsequently, Gel recovery, separation, and purification of DNA amplification products of gut microbiota will be performed according to the instructions of the QIAEX II Gel Extraction and Purification Kit operation manual. A PE library will be constructed for Illumina sequencing. Finally, the gut microbiota of patients in each group will be analyzed, including optimizing sequence information statistics and OUT analysis, counting alpha diversity index of samples, drawing dilution curve, and analyzing alpha diversity, PCoA, community composition analysis, and species difference analysis.

### 3.9. Informed Consent and Safety Assessments

All patients who have signed the written informed consent will receive appropriate treatment. Physical examinations and vital sign testing of participants are required before, during, and after treatment. Moreover, there may be some adverse reactions after acupuncture, but they are rare and slight. Acupuncture sickness may occur because of patients' physical problems or emotional stress, which can be relieved after stopping acupuncture and moxibustion and taking proper rest. Hemorrhage, hematoma, and other phenomena may occur after acupuncture, which can disappear after local pressing. Finally, during the acupuncture process, the doctor will strictly disinfect the operation. Adverse events will be recorded in detail for safety evaluation and submitted to the institutional review board (IRB).

### 3.10. Quality Control, Data Management, and Monitoring

Ahead of the recruitment and treatment of this study, the whole research team will be requested to learn in professional training classes, which guarantees the smooth progress of the plan and the sufficient understanding of the management procedure of the trial. The case report forms will preserve the treatment plans, crucial adverse reactions, and safety assessments of each patient throughout the whole process of the protocol. Besides, the case report forms will be maintained by our dedicated data management team and will be kept in a closed environment with security and access restrictions. Our research team members will ensure that all data are confidential and prevent data leakage and loss. The patients' information and records will be preserved on password-protected servers. Only the research team members are allowed to access patient information and perform data quality control. The data quality will be checked regularly by the research assistant under the monitors. The Ethics Committee of the Henan University of Chinese Medicine will monitor the data, supervise the trial, audit the trial every 3 months, and manage the progress and standardization of the trial.

### 3.11. Statistical Analysis

Data analysis will be conducted by using the IBM SPSS for Windows (Version 21.0). Basic descriptive statistics (mean and SD ($\overset{¯}{x}\pm s$)) will be reported for the characteristics and outcomes of each participant. The statistical significance is defined as *P* < 0.05 for all statistical analyses.

The Piper fatigue scale, KPS score, quality-of-life score, expression levels of HPA axis-related factors and inflammatory cytokines, and DNA copy number of gut microbiota are all measurement data. When comparing between groups, if the normal test and homogeneity test of variance are met, the *t*-test of two independent samples will be used. If it meets the normal test but does not meet the homogeneity test of variance, two independent sample-corrected *t-*tests will be used. If the normal test is not met, the Wilcoxon Man-Whitney *U* rank sum test for comparison between the two samples will be used.

The correlation analysis between gut microbiota and clinical efficacy score, HPA axis-related factors, and inflammatory cytokines will be performed using Pearson correlation analysis (for data obeying normal distribution) or Spearman correlation analysis (for data not obeying normal distribution).

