### 3.5. Sample Size

According to the results of previous literature (clinical study on an acupuncture fatigue group for cancer-related fatigue of qi and blood deficiency type), the average fatigue scale score of the control group was 5.17 ± 1.26, and the average score of the fatigue scale in the acupuncture group was 4.17 ± 1.14. In our study, we will set the following parameters: *α* = 0.05, 2-sided, power = 0.9. Our software PASS (Version 15.0) will be used to calculate the sample size of the treatment group and the control group, and the result is 30 in each group. Considering the loss of sample size caused by the 15% dropout rate, the final calculation will require at least 35 cases in the treatment group and 35 cases in the control group, and a total of at least 70 cases will be included.

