Therefore, we will choose Zusanli (ST36), Sanyinjiao (SP6), Guanyuan (CV4), Qihai (CV6), and Baihui (GV20) acupuncture points to perform acupuncture treatment on CRF patients after breast cancer chemotherapy. In our study, we will confirm that acupuncture therapy can reduce fatigue, improve the physical status, and improve the quality of life in CRF patients after chemotherapy for breast cancer. Moreover, acupuncture treatment will lead to changes in the HPA axis, and the expression level of ACTH in the serum is lower than that in the control group, while the expression level of CORT is higher than that in the control group. In addition, acupuncture treatment will reduce the expression levels of inflammatory cytokines IL-1*β*, IL-6, and TNF-*α* in the serum and further identify its effect on inflammatory cytokines and immune regulation. Finally, the changes in gut microbiota structure and genus in the acupuncture group and the control group will be observed, and further correlation analysis will be conducted with the HPA axis, inflammatory cytokines, and clinical efficacy evaluation. In all, acupuncture therapy will regulate the changes of CORT and ACTH hormone levels in the HPA axis by affecting the changes of gut microbiota and inhibiting the activation of inflammatory cytokines, and ultimately reduce the level of cancer-related fatigue in breast cancer patients.

If the primary hypothesis of this study is proven, acupuncture treatment has the potential to be used for reducing fatigue sensation and improving the quality of life of patients with breast cancer. Acupuncture therapy of traditional Chinese medicine would offer an alternative treatment modality and objective evidence for the treatment of CRF after chemotherapy for breast cancer and then alleviate the economic burden on patients and the society. Ultimately, the proposed study will also provide the clinical and theoretical bases for its extensive application of acupuncture therapy in tumor rehabilitation.

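### Section 3.11 applies unadjusted P < 0.05 to five serum markers and an unspecified number of microbiota comparisons, with no error control or formal exploratory status, although objective 2 is worded as establishing the mechanism

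*Protocol article*

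**What the plan says.** **Threshold.** Section 3.11 sets one rule: "The statistical significance is defined as *P* < 0.05 for all statistical analyses". The next paragraph puts the HPA-axis factors, the inflammatory cytokines and the gut-microbiota DNA copy number under the same between-group tests as the three clinical scales.

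**Markers.** Section 3.8.1 names five: "Human serum CORT, ACTH, IL-6, IL-1*β*, and TNF-*α* enzyme-linked immunosorbent assay kit will be used for detection".

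**Microbiota.** Section 3.8.2 ends its list of sequencing analyses with "community composition analysis, and species difference analysis". It gives no number of taxa, taxonomic level or test.

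**Standing of these outcomes.** Section 3.7 names three primary outcomes, all clinical. Markers and microbiota come under a separate heading, section 3.8, Other Outcome Measures.

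**What is expected of them.** The second objective (section 2) is worded as clarifying that acupuncture improves fatigue through flora, then cytokines, then the HPA axis. The Discussion predicts lower ACTH and higher CORT than in the control group, and states that "acupuncture treatment will reduce the expression levels of inflammatory cytokines IL-1*β*, IL-6, and TNF-*α* in the serum". For flora, the Discussion says changes will be observed and correlated with other measures; it gives no direction and names no taxon.

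**The concern.** A threshold of 0.05 per test limits the error of one test. Here it applies separately to each of five markers and to however many taxa are compared, and the results feed one of the trial's two objectives. The plan does not say how many significant results, or which, would count as support for the mechanism, so nothing in it prevents one nominally significant marker or taxon from being reported as such support. What is at stake is the mechanistic conclusion, which could rest on a chance finding even if fatigue does not improve.

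**Working it through.** **1. The plan's own figure.** The documents give no family-wise error rate. The only computed figure nearby is the sample size in section 3.5. Its error rates are "0.05, 2-sided, power = 0.9". For the active arm it assumes that "the average score of the fatigue scale in the acupuncture group was 4.17 ± 1.14". For the comparator it takes, from the same source, that "the average fatigue scale score of the control group was 5.17 ± 1.26".
- Difference: 5.17 − 4.17 = 1.00.
- Pooled SD: √((1.26² + 1.14²)/2) = 1.20.
- Normal approximation: n = 2 × (1.960 + 1.282)² × 1.20² / 1.00², which gives 31 per group after rounding up. The noncentral t gives 32.
- The plan states "the result is 30 in each group". That is within two patients, so 30 evaluable per arm is used below (35 × 0.85 = 29.75).

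The calculation uses α = 0.05 for a single fatigue comparison. It makes no allowance for further tests.

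**2. Five markers, independent, all null.**
- Any significant result, two-sided 0.05 each: 1 − 0.95⁵ = 22.6%.
- Any significant result in the predicted direction, 0.025 each: 1 − 0.975⁵ = 11.9%.

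**3. Five markers, correlated.** The markers are biologically linked, but the documents give no correlation, so a range is assumed. The figures are the probability that at least one of five equicorrelated standard normal statistics passes the cut-off of 1.96, in absolute value or in the predicted direction only.

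| Pairwise correlation | Any significant | Any significant in predicted direction |
|---|---|---|
| 0 | 22.6% | 11.9% |
| 0.3 | about 21% | about 10.5% |
| 0.5 | about 18% | about 9% |
| 0.8 | about 13% | about 6% |

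For a single test the corresponding rates are 5% and 2.5%.

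**4. Taxa.** The number m is not stated. With raw P < 0.05 and no true differences, the expected number of false differences is 0.05 × m. An expectation adds up whatever the dependence between taxa, so independence is not needed.
- m = 50: 2.5
- m = 100: 5
- m = 200: 10

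The chance of at least one false difference does depend on how the taxa are correlated. Under independence it is 1 − 0.95⁵⁰ = 92% for 50 taxa. Relative abundances from one community are not independent, so that percentage is not relied on here.

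**5. Price of adjusting the markers.** Holm's strictest step across five tests is 0.05/5 = 0.01. With 30 per arm and 80% power (noncentral t), the detectable standardized difference is about 0.74 at 0.05 and about 0.91 at 0.01. The later Holm steps are less strict, so 0.91 is the upper end.

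The correlation analyses in section 3.11 fall under the same threshold and would enlarge the family. They are not counted here.

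**The case against.** Multiplicity for non-primary outcomes is often left to an analysis plan, and a journal article condenses. That would answer a silence, but section 3.11 is not silent: it states one threshold for all analyses, and a plan that adjusted or downgraded these outcomes would have to depart from it.

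Other points on the protocol's side do stand, and they rule out several stronger readings that a reader might infer.

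- **That there is no hierarchy.** Sections 3.7 and 3.8 separate primary from other outcomes. What is missing is error control or a formal status within the lower tier.
- **That the trial sets out throughout to confirm the mechanism.** The abstract and section 3.1 speak of exploring the effect on the HPA axis and cytokines and observing the flora. In the Discussion, the verb confirm governs fatigue, physical status and quality of life. The firmer wording is that of objective 2 and the directional predictions for the markers. The protocol is therefore not consistent about the status of these outcomes.
- **That every taxon carries a directional claim and is tested at 0.05.** The predictions cover the five markers only. Taxon-by-taxon testing is inferred from the planned species difference analysis and the blanket threshold; no such test is spelled out, and section 3.4 gives the microbiota analysis to a third party.
- **That a chance marker finding is likely.** It is not: the rate for the markers alone is at most 22.6%.
- **That any one marker counts as success.** No such rule is stated. The Discussion predicts a joint pattern, and requiring all five to be significant would not inflate error. But the joint pattern is not made a criterion either, so the plan leaves the choice open.

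**Conclusion.** The point holds in a limited form. Five serum markers with predicted directions, and an unspecified number of microbiota comparisons, fall under an explicit unadjusted threshold without formal exploratory status, while objective 2 asks for a mechanistic conclusion.

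For the markers, the chance of at least one false significant result is roughly 13% to 23% over the correlations considered, or 6% to 12% in the predicted direction. These figures assume that all five nulls are true and that correlations are equal. For the taxa, 2.5 to 10 false differences are expected if 50 to 200 are tested at raw P < 0.05; that range of counts is an assumption.

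A reader might infer that the treatment conclusion itself is compromised. The documents do not support that: the Discussion rests the recommendation on fatigue and quality of life, and the marker and flora tests do not enter those comparisons. The change is worth making because it alters what the trial can say about mechanism and costs almost nothing.

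**What to change.** In section 3.11:

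1. Limit the P < 0.05 rule to the primary comparisons. How the three primaries are handled among themselves is a separate matter.
2. Label the five serum markers exploratory and report each as a between-arm estimate with a 95% confidence interval. If a significance claim is wanted, Holm-adjust across the five instead.
3. Report taxon-level between-arm differences with Benjamini-Hochberg q-values, not raw P-values.

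In section 2, word the second objective as exploring the mechanism, in line with section 3.1. Making interpretation of the markers depend on the fatigue result is optional; a mechanistic effect can be of interest without a clinical one.

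**Cost.** A few sentences and routine adjustment of P-values that will be computed anyway, with no new patients or data. The exploratory label costs no power. The Holm route raises the detectable standardized difference from about 0.74 to at most about 0.91 at 30 per arm and 80% power.

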## 3. Design and Methods

### 3.1. Trial Design and Setting

This is a randomized controlled study to explore whether acupuncture can improve fatigue symptoms of CRF patients after breast cancer chemotherapy by regulating the gut-brain axis. Seventy participants will be randomly assigned to either the acupuncture group or the primary treatment group with 35 patients in each group in a 1 : 1 ratio. Relevant tests will be tested on both groups at the baseline and after 3 weeks of the treatment. Blood and feces will be collected at the beginning and end of treatment. Piper fatigue scale, KPS score scale, and quality-of-life scale will be used to observe the changes in fatigue symptoms and quality of life of CRF patients in two groups before and after treatment and to inspect the curative effect of acupuncture on CRF. Then, the method of ELISA will be used to explore the regulatory effect of acupuncture on the HPA axis and inflammatory cytokines. Moreover, based on 16SrDNA technology, the changes in gut microbiota structure and flora of CRF patients will be observed. Ultimately, the correlation analysis of gut microbiota content can be related to inflammatory cytokines, HPA axis, and clinical efficacy evaluation (Figure 1 and Table 1).

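### The between-group tests are unadjusted for baseline, do not say whether post-treatment values or changes are compared, and let pre-tests pick the effect measure

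*Protocol article*

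**What the plan says.** Section 3.11 lists the Piper, KPS and quality-of-life scores, the hormone and cytokine levels and the gut microbiota DNA copy number as measurement data, and gives one rule for comparing the arms on all of them. It opens "When comparing between groups, if the normal test and homogeneity test of variance are met", in which case an ordinary two-sample t-test is used. If only the variance test fails, a corrected t-test is used. The last branch reads "If the normal test is not met, the Wilcoxon Man-Whitney" test. No branch includes a covariate, and none says whether the post-treatment value or the change from baseline is compared.

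The baselines exist. Section 3.1 states: "Relevant tests will be tested on both groups at the baseline and after 3 weeks of the treatment". Table 1 schedules the three scales, the blood samples and the stool samples at week 0 and again at closeout. Section 3.7 describes the primary outcomes as improvement between the two assessments.

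The sample size in Section 3.5 compares two group means and uses no baseline information: "the average fatigue scale score of the control group was 5.17 ± 1.26". Against this it sets a mean of 4.17 (SD 1.14) under acupuncture, with two-sided alpha 0.05 and power 0.9.

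**The concern.** Each patient supplies a before and an after value, and the arms are small: 35 enrolled and about 30 evaluable each. Patients who start more fatigued will tend to end more fatigued. A comparison of post-treatment scores alone therefore carries part of any chance difference at baseline and leaves explainable variation in the error term. A comparison of changes carries the imbalance the other way and can be less precise. Because Section 3.11 names neither, the analyst could choose after seeing the data.

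The test is also picked by the data, outcome by outcome. One primary outcome could be reported as a difference in means and another as a rank comparison, so the quantity being estimated is not settled in advance.

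This is not a detail left to an analysis plan. Section 3.11 states the method, and a plan that followed it would inherit it.

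**Working it through.** **Inputs from Section 3.5.** Means 5.17 and 4.17 (difference 1.00), SDs 1.26 and 1.14, two-sided alpha 0.05, power 0.90, 30 per group before dropout and 35 after. Allowing for the stated 15% dropout, 35 × 0.85 = 29.75, so about 30 per arm are evaluable.

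**Assumptions, not in the documents.** The correlation r between baseline and post-treatment score is taken as 0.3, 0.5 and 0.7. The baseline SD is taken as equal to the pooled SD from Section 3.5. The article does not say that those SDs are baseline SDs.

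**1. The plan's own figure.** Pooled SD = √[(1.26² + 1.14²)/2] = √1.4436 = 1.2015. Normal approximation: n = 2 × 1.4436 × (1.960 + 1.282)² / 1.00² = 30.3, so 31 per group; the exact noncentral t gives 32. The stated 30 is reproduced to within 2 patients, so the sample size matches an unadjusted comparison of two means. At 30 per group the standard error is 1.2015 × √(2/30) = 0.310, the noncentrality is 1/0.310 = 3.22, and the power of the t-test is 0.887.

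**2. Power at 30 per arm by analysis.** The effective SD is 1.2015 for post-treatment values, 1.2015 × √[2(1 − r)] for changes, and 1.2015 × √(1 − r²) for ANCOVA, which has 57 residual degrees of freedom in place of 58.

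| r | Post-treatment: SD, power | Change: SD, power | ANCOVA: SD, power | Variance saved by ANCOVA against post-treatment (r²) |
|---|---|---|---|---|
| 0.3 | 1.20, 0.887 | 1.42, 0.764 | 1.15, 0.913 | 9% |
| 0.5 | 1.20, 0.887 | 1.20, 0.887 | 1.04, 0.955 | 25% |
| 0.7 | 1.20, 0.887 | 0.93, 0.983 | 0.86, 0.993 | 49% |

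By the normal approximation, the number per group for 90% power falls from 31 to 28, 23 and 16.

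**3. Carry-over of a chance imbalance.** The baseline difference between arms has a standard error of 0.31 point. An imbalance of that size shifts a post-treatment comparison by r × 0.31 = 0.09, 0.16 and 0.22 point at r = 0.3, 0.5 and 0.7. It shifts a comparison of changes in the opposite direction by (1 − r) × 0.31 = 0.22, 0.16 and 0.09 point. The planned effect is 1.0 point.

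**4. The pre-test rule.** The rule was simulated with 30 per arm and 6,000 runs per setting, using Shapiro-Wilk and Levene tests at 0.05. Those two tests are an assumption, as the article does not name its own. With normal data the overall type I error was 0.049 to 0.050; with skewed (gamma) data it was 0.056. In truly normal data the rank test was still chosen in about 9 to 10% of runs and the corrected t-test in about 7 to 8%. In the skewed data the rank test was chosen in about 80%.

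**The case against.** Three stronger readings are tempting, and the documents do not support them.

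- **That baseline is ignored outright.** Section 3.11 does not say so. Section 3.7 speaks of improvement and Section 3.1 of changes before and after treatment, so a test of changes may be meant, and that uses the baseline. At r = 0.7 it also beats the unadjusted post-treatment test, 0.983 against 0.887. What stands is that the tested quantity is unstated and that neither version matches ANCOVA.
- **That chance imbalance threatens the result by 0.31 point, or 31% of the target.** That figure is the standard error of the baseline difference. Only the fraction r of it reaches a post-treatment comparison, which is 0.09 to 0.22 point. Nor is the test invalid: under randomisation it is unbiased, and its standard error already covers this variation. In the roughly 24% of simulated trials with an imbalance above 0.3 SD, its type I error was 7%, 10% and 14% at the three correlations, but over all trials it stayed near 5%.
- **That the pre-tests cost precision or inflate the error rate.** The precision loss comes from the missing adjustment. The simulated overall error rate barely moves.

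It is also fair to say that the gain depends on a correlation the article does not give. At r = 0.3 it is modest, 0.887 to 0.913.

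**Conclusion.** The point holds as one of efficiency and clarity, not validity. Section 3.11 prescribes an unadjusted comparison, leaves open whether values or changes are compared, and makes no adjustment for baselines that the trial already collects. ANCOVA has the higher power on either reading at every correlation examined: by 0.026 to 0.106 over post-treatment values, and by 0.149, 0.068 and 0.010 over changes at r = 0.3, 0.5 and 0.7. At 30 per arm it also brings power above the planned 0.90, which the unadjusted t-test narrowly misses. These figures rest on the assumed correlations and on a baseline SD of about 1.2.

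The pre-test rule is a separate and smaller matter. It leaves the effect measure undecided and possibly different between outcomes, with little effect on the overall type I error. The change is worth making, but the trial would not be unsound without it.

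**What to change.** In Section 3.11, replace the pre-test rule with one prespecified ANCOVA per continuous outcome: the post-treatment value regressed on arm and that outcome's own baseline, with robust or unequal-variance standard errors. Report the adjusted mean difference with its 95% confidence interval. Keep the rank-sum test as a sensitivity analysis. This also settles which quantity is compared.

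The documents give no distributions for the biomarkers, so they offer no ground for requiring a log transformation. If one is wanted for a skewed marker, name the marker in advance and report a ratio of geometric means for it, not a mean difference.

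The cost is one degree of freedom per model and a change of wording. Table 1 already schedules every baseline measurement needed, so no patients, visits or samples are added.

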## 2. Objectives

To observe the treatment of acupuncture in improving CRF with breast cancer after chemotherapy in patientsTo clarify that the acupuncture affects the expression level of inflammatory cytokines in the immune system by regulating the structural changes of intestinal flora, then regulates the changes of HPA axis function, and finally plays a role in improving fatigue symptoms

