### 3.7. Primary Outcomes

We have three primary outcomes for this study: assessing the improvement of fatigue, physical performance, and the quality of life in CRF patients before treatment and 3 weeks after treatment. All evaluations will be performed by two professional physicians. They will be blinded to the treatment allocation.

The Piper fatigue scale will be used to evaluate the severity of fatigue before treatment and 3 weeks after treatment. It uses a 10-point scale of numerical descriptions, including nine items. Each item is rated on a scale of 0 to 10, with 0 indicating no fatigue and 10 indicating the most severe fatigue. In addition, 1 to 3 is for mild fatigue, 4 to 6 for moderate fatigue, and 7 to 10 for severe fatigue, and the fatigue integral is the total divided by 9. Overall, the higher the scores get, the more tired patients feel.

The KPS rating scale will be used to evaluate the body function status of patients before and 3 weeks after treatment. The KPS score is the functional status rating criterion. And the higher the KPS score gets, the better the health and physical status will be. Besides, it is generally believed that the KPS score above 80 is independent, 50-70 is divided into the semi-independent level, and below 50 is a dependent score, meaning someone needs help in their life. Patients with scores greater than 80 will have better postoperative status and longer survival time.

The EORTC core quality-of-life scale will be used to evaluate patients' quality of life before treatment and 3 weeks after treatment. QLQ-C30 (V3.0) is the most widely used method in the world to measure the quality of life of cancer patients. The inventory consists of 30 questions, from five kinds of function (physiology, daily life, cognitive, emotional, and social functions), three kinds of symptoms (fatigue, pain, nausea, and vomiting) and overall health status, the overall quality of life, and another separate six (sleep, appetite, diarrhea, constipation, difficulty breathing, and economic status) to measure the patient's quality of life. All the measurements were combined to get a score, which was proportional to the quality of life of the patients.

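### Objective 2 is an ordered causal chain, but its steps are linked only by microbiota correlations under a blanket P < 0.05, which can show association but neither mediation nor order

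*Protocol article*

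**What the plan says.** Section 2 sets as the second objective to clarify that "acupuncture affects the expression level of inflammatory cytokines in the immune system by regulating the structural changes of intestinal flora", and continues "then regulates the changes of HPA axis function, and finally plays a role in improving fatigue symptoms". The Discussion (Section 4) repeats the chain twice: once as what the trial is to determine, and once as what acupuncture will do.

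Section 3.11 gives two kinds of analysis. The first is a t-test, a corrected t-test or a rank-sum test between the arms, one variable at a time, for the clinical scales, the HPA factors, the cytokines and a microbiota measure. The second is the only analysis that joins variables to each other: "The correlation analysis between gut microbiota and clinical efficacy score, HPA axis-related factors, and inflammatory cytokines will be performed using Pearson correlation analysis", or Spearman where normality fails. The threshold is general: "The statistical significance is defined as *P* < 0.05 for all statistical analyses".

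The microbiota variable in Section 3.11 is given as "DNA copy number of gut microbiota are all measurement data". Section 3.8.2 describes the assay as 16S amplification followed by sequencing ("A PE library will be constructed for Illumina sequencing"), with alpha diversity, PCoA, community composition and species differences as outputs.

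Table 1 places the scales, blood and feces at the same two visits, one before and one after treatment.

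**The concern.** A chain with a stated direction needs an analysis that speaks to direction and to what passes through each step. A pairwise correlation does neither. If the plan is followed as written, a set of significant taxon–marker correlations could be presented as having clarified a gut-brain mechanism.

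Two features of the plan make such correlations easier to find by chance. One threshold applies to every test, although sequencing can yield many features. Nothing says that treatment arm is taken into account when variables are correlated. A further difficulty is that the microbiota variable to be tested is not one that the laboratory section describes obtaining.

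**Working it through.** **1. The chain against the analyses listed**

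| Step in Objective 2 | Analysis in Section 3.11 |
|---|---|
| acupuncture → flora | between-arm test of a microbiota measure |
| flora → cytokines | pairwise correlation |
| cytokines → HPA axis | each tested between arms; nothing links the two |
| HPA axis → fatigue | each tested between arms; nothing links the two |

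The other listed correlations (flora with HPA factors, flora with clinical score) jump over intermediate steps. The last two steps of the chain have no linking analysis.

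**2. Order.** Every variable is measured together, once before and once after treatment. Which moved first cannot be observed. The Discussion itself says that the flora can affect fatigue and that fatigue can alter the flora, and a correlation cannot separate the two directions.

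**3. Chance hits.** The plan gives no figure for the mechanism analysis, so there is none to reproduce.
- Markers: 3 clinical scales (Section 3.7) + 5 serum assays (Section 3.8.1: CORT, ACTH, IL-6, IL-1β, TNF-α) = 8. This reads the clinical efficacy score as all three scales.
- Microbiota features: not given; a range is assumed.
- Expected false positives when no association exists = 0.05 × 8 × features = 0.4 × features. This expectation does not need the tests to be independent.

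| Features (assumed) | Tests | Expected chance hits |
|---|---|---|
| 1 | 8 | 0.4 |
| 10 | 80 | 4 |
| 20 | 160 | 8 |
| 50 | 400 | 20 |
| 100 | 800 | 40 |

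With about 60 completers (35 × 0.85 = 29.75, about 30 per arm), |r| of about 0.25 reaches P < 0.05.

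**4. Pooling of arms, if done.** Suppose treatment shifts a taxon and a marker by d SD each, with no link between them inside either arm. The pooled correlation then has expected size (d²/4)/(1 + d²/4). For a reference value of d, Section 3.5 gives a fatigue difference of 5.17 − 4.17 = 1.00 and a pooled SD of √((1.26² + 1.14²)/2) = 1.20, so d = 0.83 and the expected |r| is 0.173/1.173 = 0.147. Simulation with 20,000 trials and 30 per arm gave:

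| Shift in both variables | Pooled correlation significant | Adjusted for arm |
|---|---|---|
| 0 | 4.8% | 4.8% |
| 0.5 SD | 7.3% | 5.0% |
| 0.83 SD | 20.5% | 5.0% |
| 1.2 SD | 55.9% | 4.9% |

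The 0.83 SD is the planning effect for fatigue. Applying it to a taxon or a cytokine is an illustration; the protocol gives no effect size for either.

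**5. Assay against variable.** Section 3.8.2 runs from extraction and amplification to library construction, sequencing, diversity and composition. It describes no quantification step that yields copy number, yet copy number is what Section 3.11 tests.

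**The case against.** Much can be said for the plan.

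- The mechanism evidence is not correlation alone. The between-arm tests are randomised comparisons of each point in the chain, and the Discussion states expected directions against control for ACTH and CORT. This stands: a reader might infer that Objective 2 rests entirely on correlations, and Section 3.11 does not support that.
- Section 3.1 speaks of exploring, and the Discussion presents the correlations as a further step. This softens the plan but does not remove the firm causal wording of Section 2 or of the closing part of the Discussion.
- Pooling, change scores and false-discovery control are commonly left to an analysis plan. It stands that their absence from an article is no fault in itself, and that a 0.05 threshold does not exclude adjusted P values. But the protocol names the method for this objective and sets one threshold for all analyses without separating out the correlations. The point is about what those stated rules can deliver.
- The numbers depend on assumptions. This stands. A reader might infer that the reported taxa will be mostly chance findings or shared treatment effects. The documents do not support that: with one summary index only 0.4 hits are expected, the pooled inflation is small at 0.5 SD, and pooling is not stated. Within-arm correlations would avoid that inflation, though at 30 per arm they need |r| of about 0.36 and still show no mediation.
- The copy-number mismatch is a separate matter. It is, and it adds nothing to the mediation argument, but it sits in the same analysis paragraph and needs correcting.

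**Conclusion.** The concern holds in limited form. The stated method cannot deliver the stated objective: correlation among variables measured at the same two times shows neither mediation nor order, and two of the four steps have no linking analysis. That conclusion rests on the text alone and needs no assumed figure.

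The multiplicity problem is real, but its size is conditional: 0.4 expected chance hits per feature, hence 4 at 10 features and 20 at 50, if all eight markers are correlated with every feature and no association exists. The pooled-arm inflation, about 7% at 0.5 SD and 20% at 0.83 SD against 5% after adjustment for arm, is illustrative and applies only if arms are pooled. The copy-number variable does not match the described assay.

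All of this concerns the mechanism outcomes. A reader might infer that the main efficacy result is weakened; the Piper, KPS and QLQ-C30 comparisons between arms do not depend on it.

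**What to change.** 1. Reword Objective 2 and the matching sentences in the Discussion from clarifying or determining a pathway to exploring whether changes in flora, cytokines, HPA hormones and fatigue are associated. Only this change answers the mediation and order problem; the analytic changes below do not.
2. Correlate baseline-to-end changes with adjustment for arm, for example by partial Spearman correlation. If the cytokine–HPA and HPA–fatigue steps stay in the objective, list those correlations as well.
3. Apply Benjamini-Hochberg false-discovery control, at a stated rate such as 5% or 10%, across the taxon tests and the correlations, and say that the general 0.05 threshold does not apply to them unadjusted.
4. Replace DNA copy number in Section 3.11 with the quantities that the workflow in Section 3.8.2 yields: alpha diversity, a test on between-sample distance such as PERMANOVA (alongside the PCoA already planned), and log-ratio-transformed genus abundance.

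The cost is wording and a modest amount of extra analysis on the same samples and visits. The downside is that fewer taxa will be declared significant and the mechanistic claim will be weaker.
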